#### *Breastfeeding:*

We will measure the following factors in relation to breastfeeding: intention (tp0,1), trust in ability to cope with breastfeeding (tp0,1), difficulties (tp2), partner support (tp0,2), duration of exclusive breastfeeding (tp3) by single items specifically designed for this study. Feeding intention, knowledge, self-efficacy and social support are important determinants for breastfeeding initiation and duration (74), and breastfeeding is an important topic in the antenatal education in the present trial.

#### *Use of healthcare services:*

Among the parents use of health care services will be explored by examining: obstetric interventions i.e. augmentation of labour, vacuum extraction and caesarean section using data from the hospital obstetric database (Birth). Women who spend less time at home in early labour before presenting at the hospital are more likely to have an obstetric intervention (e.g. caesarean section) than those presenting in more advanced labour (75). Structured antenatal education may improve women's ability to cope at home in early labour as well as during labour resulting in less obstetric intervention (28). Additionally parental contacts to healthcare professionals for postnatal depressive symptomatology (tp2,3), and unscheduled health care contacts post discharge - i.e. contacts initiated by the mother for purposes other than a

scheduled, planned follow-up with her own health care provider for usual postnatal follow-up care - will be measured using questionnaire data (tp2).

Use of healthcare services for the child: neonatal readmissions, contacts to A&E, GP, and doctor on call in the national registers (tp4). Due to power considerations this measure will be a composite measure. Each component will also be analysed separately. According to service providers insecure parents use the healthcare services beyond indication. Janicke and Finney developed an efficacy-related model of paediatric services, suggesting that the use of these services is a function of perceived parental stress and low self-efficacy in coping with life demands (76). The Copenhagen Capital region has established an emergency phone line, and citizens are encouraged to use this when in doubt about appropriate course of action in relation to illness and accidents. Use of the emergency phone will be examined in the national registers (tp4). A program to increase knowledge on newborn care, parental self-efficacy and social network and support may affect use of healthcare services.

#### *Satisfaction with relationship and family break-ups*

Satisfaction with relationship will be measured with a scale from the Avon Longitudinal Study of Parents and Children (ALSPAC) (tp0,1,2,3,4) (77). Furthermore we will examine divorce and break-ups within the child's first year of life using the national registers (tp4).

The trajectory of marriages/relationships following the birth of a child is likely to have important implications for both long-term health of the parent's relationship and their children's development (78). Social support is important during pregnancy and childbirth and the partner is usually the main source of support. A Swedish cohort study found a higher rate of divorce among women who were unsatisfied with their partner's support during pregnancy (79). Early family transitions that strain couple relationships provide opportunities for preventive interventions to strengthen marriage (78). In the Newborn trial there is a focus on couple communication and expectations, and the importance of partner support and mutual respect and understanding.

#### *Medicine use*

Family medicine use will be recorded by use of questions from the Danish National Health survey program (tp2,3,4) (80). Some medicine is sensitive to psychosocial circumstances and may reflect a general strategy for coping with daily stressors (81-83). A high level of perceived stress is associated with use of over-the-counter medicine, primarily analgesics (82-84). Depression is also associated with excessive analgesic use (84). Administration of over the counter medications, especially analgesics, for children is common (85). Not all medicine use among children can be explained by prevalence of symptoms (85). Qualitative studies suggest that some medicine administration may be a form of "social medication," to give parents control over children's behavior that they perceive as fractious and irritating (86)

Smoking is associated with stress and will be measured by questions from the national health interview surveys.

Mental well-being: Mental health promotion and wellbeing strategies are urgent public health concerns and the need for the promotion of mental health and wellbeing has now become a feature of government policy within many countries throughout the world. It is possible that the Newborn intervention may increase mental wellbeing. It will be measured using the Warwick-Edinburgh mental well-being Scale (WEMWBS) (tp 1,2,3,4).

Intermediate measures:

When evaluating health promoting programs a number of intermediate indicators (e.g. self-efficacy, beliefs, knowledge, skills acquisition) should be used to assess various components of a program and to allow illuminative evaluation (87).

Furthermore for some particular health promotion models, intermediate indicators will serve as outcome indicators (87). For example, while evidence of self-efficacy might provide an intermediate indicator of ultimate success in terms of a reduction in risk factors for a negative outcome, self-efficacy might equally be judged as a desirable outcome in its own right for a salutogenic model of health promotion.

Central to how parents adapt to parenthood are their perceptions of having access to available resources for meeting the demands of parenthood (2, 11). Some of the most important resources related to parenting are: self-efficacy, social network and support, and parenting alliance (2, 23, 88). The Newborn antenatal education program aims to increase these resources, hence the transition to parenthood should be smoother and less stressful if the program is successful.

*Trust in own ability to cope with birth*

Will be measured using questionnaire data (tp1). Questions are developed for this trial. Structured antenatal education may improve women's trust in their ability to cope with birth resulting in e.g. lower epidural rates (28).

*Trust in own ability to cope at discharge*

Will be measured using questionnaire data (tp1). Questions are developed for this trial. Perceived readiness for discharge has become increasingly important to assess as hospital length of stay following birth has decreased - it may affect patient satisfaction, physical, emotional, psychological, and social outcomes (89).

*Parenting self-efficacy (PSE)*

To evaluate parenting self-efficacy (PSE) i.e. the individual's appraisal of his or her competence in the parenting role Salonen's PSE scale measuring parents' perceived competence in day-to-day infant care tasks, as well as interactive behaviour will be used (tp 2) (90).

High PSE is important for sense of well-being and parenting satisfaction (23, 91). PSE has been identified as an important buffer against parenting stress (23, 88), a major determinant of parenting behaviors, and closely linked to child development outcomes and psychosocial child adjustment (25, 92-94). Experience of childbirth has an impact on PSE (95-97). Findings suggest that parenting programs may improve PSE (98-101). However, studies on PSE around the time of childbirth are scarce (90, 100, 102-104), hardly any are randomised trials, sample sizes are small, and thus generalisability of findings is limited (100, 102).

#### *Trust in own ability to breastfeed*

Will be measured using questionnaire data (tp0,1). Two questions are inspired by Kronborg (26) and further developed for this trial. Trust in own ability to breastfeed is associated with breastfeeding initiation and duration (26, 27).

#### *Couple communication*

Couple communication will be measured with a scale from the Avon Longitudinal Study of Parents and Children (ALSPAC) (tp0,1,2,3,4) (77). Identifying effective ways of talking and listening is likely to improve the quality of couple communication, which in turn may increase parenting alliance and satisfaction with the relationship.

#### *Network and social support*

Social support (structure and function) will be measured by two previously well validated questions from the Danish Longitudinal Health Behaviour Study (tp0,1,2,3,4) (105) as well as by 6 questions designed for this trial (tp1,2).

Based on the literature the theoretical definition of social support for this trial is the combination of social structures and social functions, where social structures demonstrate cohesiveness and there is a flow of emotional concern, instrumental aid, information and appraisal between people (73). Functional social support has four dimensions: informational, instrumental, emotional and appraisal support. Structural social support has two dimensions: formal (health care professionals) and informal (family, friends and significant others) (73). The Newborn trial addresses all these dimensions of social support.

Previous research has shown that social support can facilitate women's transition to motherhood (106, 107), some of whom find the transition psychologically stressful (108). There is evidence that social support from staff and different kinds of hospital practices have a positive impact on parenting (97, 109, 110). In a Swedish study women dissatisfied with partner support during pregnancy experienced more physical symptoms, more depressive symptoms, more major worries and a lower sense of coherence. One year after childbirth a higher rate of divorces was found in women being dissatisfied in early pregnancy (79). Social support for first-time mothers may play an important part in both enhancing maternal parental self-efficacy and reducing postnatal depressive symptomatology in the early postpartum period (73).

*Demographic variables and individual characteristics:*

Education: In this trial, education is assessed using the International Standard Classification of Education (ISCED) (UNESCO 1997) which combines school and vocational education (tp0).

Occupational social class: The coding format used to define occupational social class in this trial is based on the coding principles used by the National Danish Centre for Social Research for many years. This format is in accordance with the social class classification of the Registrar General in the UK. The format is a five- point classification scheme (I-V). Individuals are classified based on occupational position, educational qualifications required and the number of subordinates. Individuals outside the labour market will be classified as occupational social class VI (tp0).

Marital status, cohabiting status and amount of children living in the household will be measured using standard health survey questions (tp0).

Sense of coherence will be measured using the 9 item scale developed by Setterlind and Larsson (111). This is a validated scale previously used in Danish population-based surveys as well as in a prospective survey among Danish women receiving fertility treatment (tp0,3) (112).

Self-rated health – physical and emotional (tp0,2,3,4), subjective health complaints (0,2,3,4), and long term illness (tp0) will be measured by well validated questions from the Danish National Health survey program (80).

*Measures of program implementation and use of additional antenatal and postnatal services:*

We will evaluate whether the protocol is followed in program delivery and how much of the intended program the participants are receiving. Qualitative interviews will be conducted with selected participants and program facilitators. Also participants will be asked to fill in a questionnaire following each session highlighting whether the intended subjects of the session have been covered. Group facilitators will be asked to fill in a similar questionnaire with the opportunity to explain why certain topics may have been omitted.

Measures of non-response/non participation: What proportions of the intended groups are participating in the program will be explored by examining demographic characteristics of those who declined to participate in the trial via the national registers, as well as examining characteristics of those who accepted and then did or did not show up for the sessions.

Use of additional antenatal and postnatal services will be examined via questions specifically developed for this purpose.

**Outcome assessment committee**

The reading and interpretation of the outcomes will be centralized at the Centre for Intervention research and the assessor will be blinded of the participants' intervention group.

## 6.2 Method and timing

**Table 1: Assessment tools and outcome measures**

Baseline is time point 0 (tp0) (<20 weeks gestation), 37 weeks gestation (tp1), 9 weeks (tp2), 6 months (tp3) and 1 year after expected due date (tp4).

| Tools                                                                               | Outcomes                                          | Time points  |
|-------------------------------------------------------------------------------------|---------------------------------------------------|--------------|
| Primary measure                                                                     |                                                   |              |
| Hvidovre hospital obstetric database                                                | Epidural use                                      | • Birth      |
| Secondary Measures                                                                  |                                                   |              |
| Perceived stress scale                                                              | Stress                                            | • 0,1, 2,3,4 |
| Swedish Parenthood Stress Questionnaire (SPSQ) translated into Danish               | Parenting stress                                  | • 2,3,4      |
| The Parenting alliance measure                                                      | Parenting alliance                                | • 3,4        |
| Explorative Measures                                                                |                                                   |              |
| Single item question from the Longitudinal Copenhagen City Heart Study              | Stress frequency                                  | • 0,3,4      |
| Single item question from the Longitudinal Copenhagen City Heart Study              | Stress intensity                                  | • 0,3,4      |
| 10-item Edinburgh Postnatal Depression Scale                                        | Antenatal and Postnatal depressive symptomatology | • 0,1,2      |
| MDI, ICD-10                                                                         | Depressive symptomatology                         | • 3          |
| The Hopkins Symptom Check List (SCL-25) first 10 items (anxiety score, SCL-anxiety) | Anxiety                                           | • 1,2,3      |

| Tools                                                           | Outcomes                                                                              | Time points |
|-----------------------------------------------------------------|---------------------------------------------------------------------------------------|-------------|
| Single item                                                     | Breastfeeding (intention)                                                             | • 0,1       |
| Single item                                                     | Partner support in relation to breastfeeding                                          | • 0,2       |
| Single item                                                     | Breastfeeding (difficulties)                                                          | • 2         |
| Single item                                                     | Breastfeeding (duration)                                                              | • 3         |
| Hvidovre hospital obstetric database                            | Use of healthcare services (Obstetric intervention)                                   | • Birth     |
| Danish national Registers                                       | Use of healthcare services                                                            | • 4         |
| Single item question                                            | Use of healthcare services for postnatal depressive symptomatology                    | • 2,3       |
| Single item question                                            | Use of healthcare services - maternal unscheduled health care contacts post discharge | • 2,3       |
| Scale from ALSPAC                                               | Satisfaction with relationship                                                        | • 0,1,2,3,4 |
| Danish national Registers                                       | Divorce/break-ups                                                                     | • 4         |
| Medicine use question from the National health interview survey | Medicine use                                                                          | • 2,3,4     |
| Danish national Registers                                       | Medicine use for depression                                                           | • 4         |
| Smoking question from the National health interview survey      | Smoking                                                                               | • 1,2,3,4   |
| Mental Well-being                                               | The Warwick-Edinburgh Mental Well-being Scale                                         | • 1,2,3,4   |
| Intermediate measures                                           |                                                                                       |             |

| Tools                                                             | Outcomes                                                                    | Time points |
|-------------------------------------------------------------------|-----------------------------------------------------------------------------|-------------|
| Single item questions                                             | Trust in own ability to cope with birth                                     | • 1         |
| Single item questions                                             | Trust in own ability to cope at discharge                                   | • 1         |
| Two single item questions                                         | Trust in own ability to breastfeed                                          | • 0,1       |
| Scale from ALSPAC                                                 | Communication in the relationship                                           | • 0,1,2,3,4 |
| Two questions from the Danish longitudinal Health Behaviour Study | Network and perceived social support – informal: emotional and instrumental | • 0,1,2,3,4 |
| Six questions                                                     | Network and perceived social support – formal : informational               | • 1,2       |
| Demographic and individual characteristics                        |                                                                             |             |
| ISCED                                                             | Education                                                                   | • 0         |
| Five point classification scheme - questionnaire                  | Occupational social class                                                   | • 0         |
| Four questions                                                    | Marital status, cohabiting status, children living in the household         | • 0         |
| SOC 9-item scale by Setterlind and Larsson                        | Sense of coherence                                                          | • 0,3       |
| Two single items                                                  | Self-rated health (Physical/emotional)                                      | • 0,2,3,4   |
| Questions from the National health interview survey               | Subjective health complaints                                                | • 0,2,3,4   |
| Questions from the National health interview survey               | Long term illness                                                           | • 0         |

## **7. Statistical plan and data analysis**

### **7.1. Sample size and power estimations**

Previous RCTs on antenatal parenting interventions have been difficult to interpret partly because of problems related to small sample sizes. This trial will to our knowledge be the biggest RCT on an antenatal parenting intervention to date.

#### **Sample size**

Previous data from trials (28) and hospital databases (113) indicate that the proportion of women who use epidural analgesia during birth is between 23 and 41 %. The proportion is higher among first-time mothers. Assuming that the majority of included participants in the NEWBORN trial will be first-time mothers, it is plausible to assume a proportion of epidural use of 31 % in the control group. If use of epidural analgesia can be reduced from 31 % in the control group to 25 % in the experimental group (risk reduction of 16.7 %), with a type I error (alpha) of 5 % and a type II error of 20 % (power of 80), then this requires randomisation of a total of 878 women to the intervention group and 878 women to the control group.

#### **Power estimation for the secondary outcome Perceived Stress Scale**

We are planning a trial with 878 experimental participants and 878 control participants. In a previous study the Perceived Stress Scale response within each participant group was normally distributed with standard deviation 6 (114). If the true difference in the experimental and control means is 1, we will be able to reject the null hypothesis that the population means of the experimental and control groups are equal with probability (power) 93.7%. The type 1 error probability associated with this test of this null hypothesis is 5%.

#### **Power estimation for the secondary outcome Swedish Parenthood Stress Questionnaire**

In a previous study the Swedish Parenthood Stress Questionnaire response within each subject group was normally distributed with standard deviation 0.5 (44). If the true difference in the experimental and control means is 0.1, we will be able to reject the null hypothesis that the population means of the experimental and control groups are equal with probability (power) 98.7%. The type 1 error probability associated with this test of this null hypothesis is 5%.

#### **Power estimation for the secondary outcome Parenting Alliance Measure**

In a previous study the Parenting Alliance Measure response within each subject group was normally distributed with standard deviation 20 (55). If the true difference in the experimental and control means is 4, we will be able to reject the null hypothesis that the population means of the experimental and control groups are equal with probability (power) 98.7%. The type 1 error probability associated with this test of this null hypothesis is 5%.

## 7.2 Statistical methods

Reporting will follow the guidelines of the CONSORT-statement. Statistical analyses will be intention to treat as well as per protocol. The level of significance will be 0.05.

The analysis of the primary binary outcome will be done using the generalised linear mixed model with distribution = binomial, link = logit.

If the percent missing cases > 5%, the results of this analysis will be subjected to a 'worst case' and a 'best case' scenario analysis of the potential impact of missing values. Assume a beneficial effect (less use of epidural analgesia) is noted in one group (group A) as compared to the other group (group B). A worst case scenario will then be constructed where missing values in group A are imputed by a "yes" to use of epidural analgesia and missing values in group B are imputed by a "no" to use of epidural analgesia. A corresponding best case scenario will also be constructed and the result under both scenarios will be computed.

Analyses (adjusted by baseline value and protocol specified variables) of perceived stress at 37 week gestation and for each of the other two secondary outcomes of the area under the curve (AUC) from 9 weeks to one year after due date will be done.

If the percent missing cases of an outcome is >5% and p of Little's test (1) < 5%, a number of datasets with observed values and predicted unobserved values necessary to produce an efficiency > 99% will be produced using multiple imputations (SAS version 9.3 or later)(2). The primary analysis will then be that based on these data sets.

Multiplicity will be dealt with as follows: the primary outcome will be tested at the 5% level. The p values of the remaining four tests will be adjusted using Hommel's procedure (Konietschke, 2012). In all events all observed p values will be reported.

For the secondary outcome measure 'Perceived Stress Scale' it will be tested using the general linear univariate model, whether the mean values differ between the two intervention groups at time 1 (37 week gestation), time 2 (9 weeks following birth), time 3 (6 months following birth), and time 4 (12 months following birth).

For the secondary outcome measure 'Swedish Parenthood Stress Questionnaire' it will be tested using the general linear univariate model, whether the mean values differ between the two intervention groups at time 2 (9 weeks following birth), time 3 (6 months following birth), and time 4 (12 months following birth).

For the secondary outcome measure 'Parenting Alliance Measure' it will be tested using the general linear univariate model, whether the mean values differ between the two intervention groups at time 3 (6 months following birth), and time 4 (12 months following birth).

The unadjusted analyses are the primary analyses. If possible all analyses will be repeated adjusted for the protocol specified stratification variable and the baseline value.

Three explorative subgroup analyses may be conducted in each case provided the subgroup interacts significantly with the intervention.

In addition to analyses performed for individuals, descriptive analyses reporting the interdependency within the couple as well as within the specific antenatal education group, and at the facilitator level will be performed by intraclass correlation.

Process evaluation will be conducted with a mixed methods approach using quantitative questionnaire data and qualitative interviews with participants and service providers. We will examine program fidelity, e.g. whether the protocol is followed in program delivery, and how much of the intended program the participants are receiving, as well as program reach e.g. what proportions of the intended groups are participating in the program, as these factors have an impact on the effect of an intervention(33). The incremental societal cost of the intervention will be computed and compared to the measured outcomes in a cost-effectiveness analysis. Direct health care costs and productivity cost in terms of labour market participation and short term absence will be calculated.

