#### Secondary outcomes:

Stress:

*The perceived stress scale* (PSS) will be used to measure global levels of perceived stress (tp 0,1,2,3,4). The PSS takes into account the individual's ability to cope (40). The scale was developed on the basis of appraisal theory (18) and was designed to “ . . . tap the degree to which respondents found

their lives unpredictable, uncontrollable, and overloading” (40). The PSS is widely cited, has been used in several studies of life stress, and has been translated into several languages. The PSS has been found to predict many adverse health outcomes (41). There has been some concern that psychological symptoms and the PSS may overlap in item content (40). However, the PSS has been shown to prospectively predict health outcomes independent of psychological symptoms (40, 42), supporting the discriminate validity of the PSS with regard to psychological symptoms (43). Despite limitations inherent in stress response measures and cautionary concerns about confounding with psychological symptoms, overall the PSS possesses good psychometric qualities and a respectable record of validity studies (41).

Parenting stress will be measured using *the Swedish Parenthood Stress Questionnaire* (SPSQ) (44) translated into Danish (tp2,3,4). The scale takes into account the individual's ability to cope and assesses parental stress with a sum score and subscale scores of incompetence, role restriction, social isolation, spouse relationship and health problems (44). Results from SPSQ have been related to physiological and psychological health, and socioeconomic and lifestyle factors (45). Furthermore significant correlations between SPSQ and clinical assessments of maternal stress and parental problems in responding to their child have been found (45).

Parenting stress has been shown to relate to negative child, parent, and family aspects e.g. lack of maternal emotional availability (46), maternal hostility (46), insecure child attachment (47, 48); parents' use of undesirable managerial techniques, (49) and more strict disciplinary style (50); child abuse and neglect, (51); depression in mothers, (52, 53), and poor marital quality (54).

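### If Little's test is not significant, nothing is imputed, and an AUC that needs all three parenting-stress questionnaires leaves out women with partial scores

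*Protocol*

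**What the plan says.** Section 7.2 (Statistical methods) of the protocol fixes three things for the SPSQ.

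- **Summary measure.** An analysis is planned "for each of the other two secondary outcomes of the area under the curve (AUC) from 9 weeks to one year after due date". The SPSQ is one of those two outcomes.
- **Visit tests.** "For the secondary outcome measure 'Swedish Parenthood Stress Questionnaire' it will be tested using the general linear univariate model", at 9 weeks, 6 months and 12 months. No repeated-measures model is named.
- **Missing data.** The rule begins "If the percent missing cases of an outcome is >5% and p of Little's test (1) < 5" (per cent). If both conditions are met, the number of datasets "necessary to produce an efficiency > 99% will be produced using multiple imputations (SAS version 9.3 or later"). "The primary analysis will then be that based on these data sets". No imputation is described for the case where either condition fails. The best-case and worst-case analysis in the same section concerns epidural use only.

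The measurement description in section 6.1 and Table 1 in section 6.2 both give three SPSQ time points ("translated into Danish (tp2,3,4"), with no baseline score. Section 7.1 bases secondary power on full data: "We are planning a trial with 878 experimental participants and 878 control participants", with the SPSQ "normally distributed with standard deviation 0.5 (44").

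**The concern.** An individual AUC from 9 weeks to one year, computed directly from the three scores, exists only for a woman who returned all three questionnaires. Section 3.8 expects non-response, since it plans two e-mail reminders and a phone call. Whether a partly observed series is used therefore depends on the imputation rule, and that rule depends on Little's test.

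If the test is not significant, two things follow.

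- **Lost precision.** Even if data really are missing completely at random, so that a complete-case AUC is unbiased, scores already collected are thrown away.
- **Unproven assumption.** A non-significant test is not evidence that data are missing completely at random. It may only mean that the departure was too small, or of the wrong kind, to be detected.

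In that branch the AUC test and the visit tests also rest on different sets of women, so they need not agree.

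**Working it through.** **1. The plan's own figure.** Section 7.1 gives 878 per arm, difference 0.1, SD 0.5 and alpha 5% (two-sided reproduces). SE = 0.5 × √(2/878) = 0.0239, and power = Φ(0.1/0.0239 − 1.96) = 98.7%. This matches the stated figure. It is a single-score calculation with every woman observed.

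**2. The AUC as a contrast.** Take the visits as weeks 9, 26 and 52, a span of 43 weeks. The trapezoid weights are (26−9)/2/43 = 0.198, (52−9)/2/43 = 0.500 and (52−26)/2/43 = 0.302. Divided by its span, the AUC is this weighted mean of the three visit scores, so the arm difference in AUC is the same weighted sum of the visit differences.

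**3. Assumptions.** The documents give no non-response rate and no correlation. Assumed here: correlation 0.6 between any two visits, and non-response at 9 weeks, 6 months and 1 year of either 10/15/20% or 20/25/30%. Each is run as pure drop-out (a woman who stops never returns) and as misses that are independent between visits.

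**4. Share of women with an AUC.**
- Drop-out: 80% or 70%.
- Independent misses: 0.90 × 0.85 × 0.80 = 61.2%, or 0.80 × 0.75 × 0.70 = 42.0%.

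**5. Precision.** With weights w and correlation matrix R, complete data give w′Rw = 0.752, so SE = 0.5 × √(2 × 0.752/878) = 0.0207. This is below 0.0239 because an average of three scores varies less than one score. For complete cases, divide the variance by the share in step 4. For the repeated-measures model, sum the information over all missing-data patterns, invert, and apply w. Efficiency is relative to complete data. The SE ratio is √(model efficiency / complete-case efficiency). Power is for a constant difference of 0.1, 878 per arm, two-sided 5%, before the Hommel adjustment.

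| Non-response | Pattern | Efficiency, complete-case | Efficiency, model | SE ratio | Power, complete-case | Power, model |
|---|---|---|---|---|---|---|
| 10/15/20% | drop-out | 0.800 | 0.876 | 1.05 | 99.1% | 99.5% |
| 20/25/30% | drop-out | 0.700 | 0.776 | 1.05 | 98.1% | 98.9% |
| 10/15/20% | independent | 0.612 | 0.947 | 1.24 | 96.6% | 99.7% |
| 20/25/30% | independent | 0.420 | 0.900 | 1.46 | 87.9% | 99.6% |

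Worked example, last row: 1.46 = √(0.900/0.420).

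**6. Sensitivity.** With equal miss rates of 5% to 30% per visit, independent, and correlations of 0.4 to 0.8, the complete-case variance is 1.14 to 2.70 times that of the model. With cumulative drop-out of 10/20/30% or 20/30/40% it is 1.16 to 1.29 times.

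**7. Bias, as an illustration only.** In a large simulated sample, the true AUC difference was −0.10 and about 35% of series were incomplete.
- Missing completely at random: complete cases and the likelihood model both gave −0.10.
- Later misses depending on the 9-week score in one arm only: complete cases gave −0.16, the likelihood model −0.10.
- The same dependence in both arms: complete cases gave −0.095.

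Dependence as strong as in the one-arm case would probably make Little's test significant at this trial's size, and imputation would then follow. The example shows the mechanism and is not a forecast of bias in the branch at issue.

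**The case against.** The strongest reply is that the protocol already has a remedy. In every scenario above, 20% to 58% of women lack an AUC, so the 5% condition is met and only Little's test stands between the plan and imputation. Once imputation is triggered, a woman with a partial series stays in, and an imputation model that uses her other scores recovers roughly what a repeated-measures model would. That is correct. A reader might infer from the AUC wording alone that anyone who misses one questionnaire is always lost. The documents do not support that, because the loss is confined to the branch without imputation.

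Other parts of the reply also stand.

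- The protocol does not say how an AUC is formed from a partial series. The need for all three scores is inferred from the definition of an AUC, and the statistical analysis plan may add a rule.
- A reader might think that the separate visit models drop women too. They do not: each uses every score from its own visit and only ignores the other visits.
- The 87.9% is the worst of four assumed cases. Fully independent misses are extreme, since non-response tends to cluster in the same women. Under drop-out the power loss is under one percentage point, and even the worst case exceeds 80%. If the 2350 women in the abstract are randomised (1175 per arm), the worst case is 95.2%.
- The choice between an AUC with imputation and a mixed model is between accepted methods.

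One thing is not answered. When more than 5% is missing and Little's test is not significant, the protocol prescribes no imputation, and collected scores go unused on the strength of a test that cannot confirm the assumption it is used for.

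**Conclusion.** The point holds for one branch of the plan: SPSQ data missing in more than 5% and Little's test not significant. There, an AUC that needs all three scores discards women with one or two scores. On the assumed inputs, the standard error is about 5% too large under drop-out and 24% to 46% too large with independent misses. The power cost for a difference of 0.1 ranges from 0.4 to 11.7 percentage points (99.5 − 99.1 and 99.6 − 87.9). When imputation is triggered, the gain from changing is close to nil.

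These sizes rest on an assumed correlation, assumed non-response, 878 per arm and the inferred three-score rule. No bias is established for this trial. This is a cheap improvement to a secondary analysis, worth making before data are analysed, and it does not touch the epidural outcome.

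**What to change.** In section 7.2, analyse the SPSQ, and any other outcome given an AUC, with one linear mixed model for repeated measures: arm, visit, arm-by-visit and unstructured covariance, on all women with at least one postnatal score. Test the AUC as the pre-specified time-weighted contrast of the visit differences (weights as in step 2 for the SPSQ), and take the per-visit differences from the same model. State that this does not depend on Little's test. The quantity tested is still the AUC difference, and the overall and per-visit results then rest on the same women.

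The cost is wording and a few lines of code, with no new data. It is not free of assumptions, as a reader might suppose: the model assumes data are missing at random, the covariance structure must be stated, and women with no postnatal score do not contribute, although imputation could retain them.
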